### Objectives

This study aims to investigate skin barrier function in PI-prone and affected anatomical sites among ICU patients using non-invasive assessments of TEWL, skin pH, stratum corneum hydration and local skin temperature. Specifically, the study will evaluate longitudinal changes in skin barrier parameters, compare patients with and without PIs, examine relationships between biophysical measurements, identify clinical and physiological determinants of skin barrier dysfunction and explore differences according to PI stage and anatomical location.

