### Measurement devices

Skin barrier function parameters will be assessed using non-invasive biophysical measurement devices. All devices are certified, used in clinical and academic research, and do not compromise skin integrity or patient comfort (table 2).

**Table 2 T2:** Standardised measurement procedures for skin barrier function assessments

Parameter	Device	Anatomical sites	Measurement procedure	Unit
Transepidermal water loss (TEWL)	Vapometer (Delfin Technologies)	Sacrum, right and left trochanters, right and left scapular regions, right and left lateral lower extremities, posterior neck, corresponding control sites and PI-affected skin	Probe positioned perpendicular to the skin surface according to manufacturer recommendations	g/m²/h
Stratum corneum hydration (SCH)	MoistureMeterSC (Delfin Technologies)	Same sites as above	Probe applied using standardised contact pressure according to manufacturer recommendations	Arbitrary Units (AU)
Skin pH	PH5F pocket pH Meter (Apera Instruments)	Same sites as above	Flat electrode gently applied to the skin until a stable reading is achieved	pH units
Local skin temperature	Integrated temperature sensor of the Vapometer	Same sites as above	Recorded simultaneously during TEWL assessment	°C

Standardisation procedures.

✓ Measurements performed by trained researchers using a standardised protocol.

✓ Devices calibrated according to manufacturer recommendations before data collection sessions.

✓ Non-invasive assessment procedures used for all measurements.

✓ Identical measurement procedures applied across all anatomical sites and time points.

✓ Assessments performed within the first 4 hours of ICU admission, at 24, 48, 72 and 96 hours, on day 14, and weekly thereafter until ICU discharge.

✓ Corresponding control sites assessed alongside all PI-prone and affected anatomical sites.

✓ TEWL values calculated as the mean of two consecutive measurements.

✓ Measurements recorded immediately in the study database following assessment.

✓ Device probes cleaned and disinfected between patients using hospital-approved disinfectants in accordance with institutional infection prevention policies and manufacturer recommendations.

✓ Pressure injury sites assessed using the same standardised procedures, with measurements obtained from peri-wound skin when direct measurement of the wound bed is not appropriate.

PI, Pressure Injury.

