#### Data collection methods

Biophysical measurements will be obtained from anatomical regions commonly identified as PI-prone sites in critically ill patients, including the sacrum, bilateral trochanters, bilateral lateral lower extremities, bilateral scapular regions and the posterior neck.

A repeated-measures approach will be used to evaluate both short-term and longitudinal changes in skin barrier function. This approach was selected based on previous studies in which repeated biophysical assessments were successfully applied to monitor temporal changes in skin integrity over time.^18
33–35^ The initial assessment will be performed within the first 4 hours of ICU admission. Subsequent measurements will be conducted at 24, 48, 72 and 96 hours, on day 14, and weekly thereafter until ICU discharge (table 2).

For each anatomical measurement site, a corresponding control area located approximately 10 cm away will also be assessed. To ensure consistency across repeated measurements, predefined circular measurement areas will be marked and used throughout follow-up.

All measurements will be conducted by trained researchers according to a standardised protocol. During each measurement session, one researcher will perform the measurements, a second researcher will verify the readings and a third researcher will record the data electronically. Paper-based forms will be available as a backup in case of technical issues.

If a PI develops, measurement procedures will be adapted according to injury stage. For Stage I PIs, measurements will be obtained directly from the affected site. For Stage II or more advanced PIs, measurements will be performed on the nearest adjacent area of intact skin. In both situations, the corresponding control site will also be assessed. Wound progression will be monitored using the Bates-Jensen Wound Assessment Tool.

To minimise the influence of mechanical loading, measurements will be performed following routine patient repositioning and approximately 15–20 min after pressure removal. All anatomical regions, except the sacrum, will be assessed bilaterally.

The duration of each measurement is approximately 15–20 s for most devices, whereas pH measurements require approximately 30 s for stabilisation. If haemodynamic instability occurs during the procedure, measurements will be immediately discontinued to ensure patient safety.

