#### Statistical analysis

Statistical analyses will be performed using IBM SPSS Statistics V.29.0 and, where required for time-to-event analyses, R statistical software.

Descriptive statistics will be used to summarise demographic, clinical and skin barrier function characteristics. Prior to inferential analyses, data will be examined for completeness, outliers and distributional assumptions. Continuous variables will be assessed for normality using visual inspection methods (histograms and Q–Q plots) and the Shapiro-Wilk test. Descriptive statistics will be reported as mean and SD or median and IQR, as appropriate. Continuous variables will be reported as mean and SD or median and IQR, as appropriate, whereas categorical variables will be presented as frequencies and percentages.

Changes in TEWL, SCH, skin pH and local skin temperature over time will be examined using repeated-measures analyses. To account for repeated observations within individuals and varying follow-up durations, linear mixed-effects models will be used as the primary analytical approach.

Comparisons between patients who develop PIs and those who do not will be performed using appropriate parametric or non-parametric methods according to data distribution. For patients who develop PIs, measurements obtained from affected sites will be compared with corresponding control sites using paired analyses.

The association between longitudinal skin barrier function parameters and incident PI development will be evaluated using discrete-time survival analysis. Follow-up will be divided according to the predefined skin assessment intervals, thereby accounting for the interval-censored nature of PI onset. TEWL, SCH, skin pH and local skin temperature will be incorporated as time-varying covariates using the most recent measurement available for each assessment interval. Death and ICU discharge before PI development will be considered competing events and will be explicitly accounted for in the time-to-event analyses. Potential determinants, including demographic characteristics, illness severity, PI risk scores, laboratory findings, treatments and nursing care practices, will first be examined in univariable analyses. Multivariable models will subsequently be constructed using a limited number of prespecified clinically relevant covariates, according to the number of observed PI events, to minimise model overfitting.

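### Stage I injuries are read on the lesion but Stage II+ injuries on neighbouring skin, and the paired site-control comparison keeps any pre-existing site difference, so both contrasts mix location with injury

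*Protocol article*

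**What the plan says.** All places are in the protocol article.

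- **Data collection methods**, Stage I: "For Stage I PIs, measurements will be obtained directly from the affected site". Stage II and above: "For Stage II or more advanced PIs, measurements will be performed on the nearest adjacent area of intact skin". The control is read in both cases.
- The same section defines the control: "For each anatomical measurement site, a corresponding control area located approximately 10 cm away will also be assessed". It also has the measurement circles marked in advance and kept for the whole of follow-up.
- **Measurement devices**, Table 2 notes: injury sites follow the standard procedure, with "measurements obtained from peri-wound skin when direct measurement of the wound bed is not appropriate". No stage cut is given. Another note reads: "Identical measurement procedures applied across all anatomical sites and time points".
- **Objectives**: one aim is to "explore differences according to PI stage and anatomical location".
- **Statistical analysis**: for patients who develop an injury, "measurements obtained from affected sites will be compared with corresponding control sites using paired analyses". No baseline term is named for this contrast. The linear mixed models in that section are stated for change over time.
- **Eligibility criteria** and **Table 1**: skin must be intact at ICU admission, and all four barrier parameters are read at 0-4 hours. Each site and its control are therefore measured before any injury.

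**The concern.** Under the stage rule every Stage I value comes from lesion skin and every Stage II+ value comes from skin beside a lesion. The two sets do not overlap, so no model can tell an effect of stage from an effect of where the probe was placed. If a lesion progresses from Stage I to Stage II, or is first seen at Stage II, the reading moves off the marked circle, and the fitted trajectory takes in a step that is partly a change of place. The article lists the assessment of change before and after injury among its strengths.

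The two descriptions of the rule also differ. A researcher following Table 2 could read a Stage II wound bed when judged appropriate; one following Data collection methods could not.

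The paired comparison has a related weakness. Pairing within a patient cancels what the two spots share. It does not cancel a fixed difference between skin over a pressure-prone site and skin about 10 cm away. Such a difference would be counted as part of the injury effect, in either direction.

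**Working it through.** **1. The plan's own figure.** Inputs from Participants and sampling: hydration 17.7 (SD 3.78) versus 20.0 (SD 3.92) AU, d = 0.59, two-sided 0.05, 90% power, ratio 1:2.

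- Difference 20.0 - 17.7 = 2.3 AU. Root-mean-square SD = √((3.78² + 3.92²)/2) = 3.85, so d = 0.597. Weighting the SDs by group size gives 0.594. The stated 0.59 is consistent.
- Two-sample t test with 46 and 92: noncentrality 0.59 × √(46×92/138) = 3.27, df 136, power 0.9005. The 138 reproduces. This point does not dispute it; only the 46 expected injury cases and the 0.59 are used below.

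**2. Paired comparison with no injury effect.** Let g be the pre-existing site-control gap in SDs of the paired difference. The documents do not give g, so it is an assumption. With n = 46 the noncentrality is g√46 = 6.78g, df 45.

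| Assumed g | Noncentrality | Significant at 0.05 |
|---|---|---|
| 0 | 0 | 5.0% |
| 0.1 | 0.68 | 10.2% |
| 0.2 | 1.36 | 26.4% |
| 0.3 | 2.03 | 51.2% |
| 0.5 | 3.39 | 91.3% |

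Testing the change in the gap since 0-4 hours removes any constant g and returns the rate to 5%, provided the same spot is read both times.

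**3. Stage contrast with no stage effect.** Assume the lesion effect is 0.59 SD at every stage, adjacent skin keeps a fraction f of it, and the 46 cases split 23/23. The value 0.59 is borrowed from the between-patient planning difference; the split and f are assumptions. Apparent stage difference = 0.59(1 - f); standard error = √(1/23 + 1/23) = 0.295; df 44.

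| Assumed f | Apparent stage difference (SD) | Significant at 0.05 | Pooled affected-site effect (SD) |
|---|---|---|---|
| 1 | 0 | 5% | 0.59 |
| 0.75 | 0.15 | 8% | 0.52 |
| 0.5 | 0.30 | 17% | 0.44 |
| 0.25 | 0.44 | 31% | 0.37 |
| 0 | 0.59 | 50% | 0.30 |

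The last column is 0.5 × 0.59 + 0.5 × f × 0.59. Pooling on-lesion and adjacent readings as one affected-site value dilutes a real effect as well.

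**4. What is and is not touched.** Readings taken before injury come from the marked circles whatever stage follows. Contrasts among Stage II+ lesions all use adjacent skin, provided the Data collection methods rule is the one followed. Neither carries the stage-location confounding.

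**The case against.** - *Reading beside an open wound may be unavoidable, and the article states the adaptation openly.* This stands. The fault lies in treating such readings as comparable with on-lesion Stage I readings.
- *The stage aim is exploratory, and no Stage I versus II+ test is written into the statistical section.* This stands and limits the weight of the point. A reader might infer that the stage objective cannot be answered at all. The documents do not support that: contrasts within Stage II+ and pre-injury readings grouped by later stage remain usable.
- *The words on paired analyses do not exclude a baseline adjustment, and an article may leave that to a fuller plan.* This is largely right. A reader might infer that a raw paired test on one visit, ignoring several lesions per patient, has been chosen; the article does not say so. What remains is that the comparison as described does not isolate injury from place, while the reading that would do so is already scheduled.
- *An analysis plan could settle the rest.* Not for the stage contrast: an adjacent-skin reading never taken at Stage I cannot be recovered later.
- *Table 2 can be read as the general rule and identical procedures as device technique only.* This is possible, but the two texts still leave the operator different discretion at Stage II and above.
- *The magnitudes are assumed.* This is correct. A reader might take d = 0.59 as the expected spurious stage gap. That is the extreme case, in which adjacent skin carries none of the effect, and the 2.3 AU behind it is a difference between patients, not between lesion and adjacent skin.

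**Conclusion.** The point holds in a limited form. A Stage I versus Stage II+ comparison of barrier parameters is confounded with reading location by the measurement rule itself, and a site's trajectory can jump when the probe is moved. The two descriptions of that rule need reconciling. The paired affected-versus-control comparison, as stated, leaves in any constant difference between the site and its control.

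The size of either bias cannot be known from the documents, which give no site-control gap and no lesion-adjacent gap. Over the assumed ranges the consequences run from slight (10% false positives at a 0.1 SD gap; a 0.15 SD spurious stage difference) to serious (91% at 0.5 SD; a 0.59 SD stage difference, found significant in half of studies). Recruitment had not started when the article was submitted, so the missing reading could still be added to the measurement procedure.

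**What to change.** 1. Make Table 2 and Data collection methods state one rule for where the probe goes at each stage.
2. At each Stage I lesion, add a reading on adjacent intact skin with the same devices, and use only adjacent readings for Stage I versus II+ contrasts. If this is not adopted, label Stage II+ readings as peri-lesional and neither pool nor compare them with on-lesion Stage I readings.
3. Record the reading location (marked circle on intact skin, lesion, adjacent), so that trajectories are not read across a change of spot.
4. Analyse affected minus control as change from the same site's 0-4 hour difference, with lesions and visits nested within patient. Make this the main result for Stage I, where the marked spot is re-read. Report Stage II+ separately, with the caveat that the adjacent spot may not be the baseline circle, so subtraction there is not clean.

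Cost: the added reading takes two TEWL measurements and one hydration measurement at 15-20 s each, plus about 30 s for pH, with temperature taken alongside TEWL: 3 × 15 + 30 = 75 s to 3 × 20 + 30 = 90 s per Stage I lesion visit. Beyond that, the cost is one field on the form and some analysis wording. The baseline readings are already scheduled.

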#### Data management

Each participant will be assigned a unique study identification number to ensure confidentiality. Personal identifiers will be removed from the analytical dataset and stored separately from study data in password-protected files accessible only to the principal investigator.

Data will be recorded using standardised case report forms and subsequently entered into a secure electronic database. Double-checking procedures will be performed regularly to verify data accuracy and completeness. Any inconsistencies identified during data entry will be reviewed against the original source documents and corrected where necessary.

All electronic data will be stored on password-protected institutional computers with regular backup. Paper-based study documents, including informed consent forms and source data, will be stored in locked cabinets within the research institution. Study records will be retained in accordance with institutional policies and applicable data protection regulations.

Only authorised members of the research team will have access to the study database. Data handling and storage will comply with national regulations and the principles of Good Clinical Practice.

#### Statistical analysis

Statistical analyses will be performed using IBM SPSS Statistics V.29.0 and, where required for time-to-event analyses, R statistical software.

Descriptive statistics will be used to summarise demographic, clinical and skin barrier function characteristics. Prior to inferential analyses, data will be examined for completeness, outliers and distributional assumptions. Continuous variables will be assessed for normality using visual inspection methods (histograms and Q–Q plots) and the Shapiro-Wilk test. Descriptive statistics will be reported as mean and SD or median and IQR, as appropriate. Continuous variables will be reported as mean and SD or median and IQR, as appropriate, whereas categorical variables will be presented as frequencies and percentages.

Changes in TEWL, SCH, skin pH and local skin temperature over time will be examined using repeated-measures analyses. To account for repeated observations within individuals and varying follow-up durations, linear mixed-effects models will be used as the primary analytical approach.

Comparisons between patients who develop PIs and those who do not will be performed using appropriate parametric or non-parametric methods according to data distribution. For patients who develop PIs, measurements obtained from affected sites will be compared with corresponding control sites using paired analyses.

The association between longitudinal skin barrier function parameters and incident PI development will be evaluated using discrete-time survival analysis. Follow-up will be divided according to the predefined skin assessment intervals, thereby accounting for the interval-censored nature of PI onset. TEWL, SCH, skin pH and local skin temperature will be incorporated as time-varying covariates using the most recent measurement available for each assessment interval. Death and ICU discharge before PI development will be considered competing events and will be explicitly accounted for in the time-to-event analyses. Potential determinants, including demographic characteristics, illness severity, PI risk scores, laboratory findings, treatments and nursing care practices, will first be examined in univariable analyses. Multivariable models will subsequently be constructed using a limited number of prespecified clinically relevant covariates, according to the number of observed PI events, to minimise model overfitting.

Inter-rater agreement for PI risk assessments and PI classification will be evaluated using Cohen’s kappa coefficient. In addition to statistical significance, effect sizes will be reported to facilitate interpretation of the clinical relevance of findings. Statistical significance will be set at p<0.05.

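### Affected-versus-control sites are to be compared by paired analyses, but the design can give several correlated pairs per patient, which an ordinary paired test does not handle

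*Protocol article*

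**What the plan says.** All references are to the protocol article.

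- **Method for this contrast (Statistical analysis).** For patients with a PI, "measurements obtained from affected sites will be compared with corresponding control sites using paired analyses". The sentence before it, on patients with and without PI, offers a choice between parametric and non-parametric methods. The test, the visit and the unit (patient, lesion or lesion at a visit) are not named.
- **Method for change over time (same section, preceding paragraph).** "To account for repeated observations within individuals and varying follow-up durations, linear mixed-effects models will be used as the primary analytical approach". This follows a sentence about changes in the four skin parameters over time and does not mention affected and control sites.
- **Sites (Data collection methods).** There are eight, "including the sacrum, bilateral trochanters, bilateral lateral lower extremities, bilateral scapular regions and the posterior neck". "For each anatomical measurement site, a corresponding control area located approximately 10 cm away will also be assessed".
- **Visits (Data collection methods).** After the baseline reading, "Subsequent measurements will be conducted at 24, 48, 72 and 96 hours, on day 14, and weekly thereafter until ICU discharge".
- **After a PI develops (Data collection methods).** For Stage I the lesion itself is measured; from Stage II on, neighbouring intact skin is measured. "In both situations, the corresponding control site will also be assessed". The notes to Table 2 (Measurement devices) agree: "Corresponding control sites assessed alongside all PI-prone and affected anatomical sites".
- **Significance (Statistical analysis).** "Statistical significance will be set at p<0.05".

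**The concern.** Pairing removes what the affected site and its control share at one reading. It does nothing about the correlation between one lesion's difference at 48 hours and the same lesion's difference at 72 hours, or between two lesions in one patient. The protocol recognises this kind of dependence when it justifies the mixed model, then names a different method for a contrast that has the same dependence.

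Because the sentence follows directly on a choice between parametric and non-parametric methods, its natural reading is a paired t-test or Wilcoxon test. Such a test leaves two main routes. Pooling all pairs overstates the number of independent observations, giving standard errors that are too small and too many false positives. Keeping one pair per patient is valid but sets aside readings that the schedule has paid for.

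**Working it through.** **1. The plan's own figure.** The article gives no calculation for the affected-versus-control contrast. Its only sample size (Participants and sampling) is for a between-patient comparison of sacral hydration. With d = 0.59, two-sided 0.05, 90% power and 1:2 allocation, a two-sample t-test needs 46 + 92 = 138 (power 0.9005), as stated. That figure does not depend on this point. It is used here only for the planned minimum of 46 patients with PI.

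**2. How several pairs arise.** A PI first seen at 48 hours gives pairs at 48, 72 and 96 hours, so three pairs if the patient stays. A second lesion over the same period would make six.

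**3. Inputs that the article does not give (assumed).**
- m, pairs per patient: 2 to 4, with 6 as an extension.
- ρ, within-patient correlation of the affected-minus-control difference: 0.3 to 0.7, with 0.1 as a low case.

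**4. Formula if all pairs are pooled as independent.** The variance of the mean difference is inflated by 1 + (m − 1)ρ. The true error of a nominal 5% test is then

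2 × [1 − Φ(1.96 / √(1 + (m − 1)ρ))].

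For ρ = 0.5:
- m = 2: inflation 1.5; 1.96/√1.5 = 1.60; error 11.0%.
- m = 3: inflation 2.0; 1.96/√2.0 = 1.39; error 16.6%.
- m = 4: inflation 2.5; 1.96/√2.5 = 1.24; error 21.5%.

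| Pairs per patient | ρ = 0.1 | ρ = 0.3 | ρ = 0.5 | ρ = 0.7 |
|---|---|---|---|---|
| 1 | 5.0% | 5.0% | 5.0% | 5.0% |
| 2 | 6.2% | 8.6% | 11.0% | 13.3% |
| 3 | 7.4% | 12.1% | 16.6% | 20.6% |
| 4 | 8.6% | 15.5% | 21.5% | 26.6% |
| 6 | 11.0% | 21.5% | 29.5% | 35.6% |

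Over m = 2–4 and ρ = 0.3–0.7 the error runs from 8.6% to 26.6%. Standard errors are too small by a factor of √1.3 = 1.14 to √3.1 = 1.76.

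**5. Simulation check.** A one-sample t-test on the pooled differences (46 patients, 8,000 runs per setting) agreed with the table within about 1 point. When the number of pairs varied between patients, as it would with differing lengths of stay, the rates were 0.3 to 5 points higher.

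**6. Readings without this inflation.**
- One summary difference per patient: simulated error 4.5% to 5.5% in every setting.
- A separate test at each visit with one lesion per patient: each test keeps 5%. The issue is then multiplicity: 1 − 0.95⁵ = 22.6% for five tests if they were independent.

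**The case against.** The strongest reply is that the article never commits to a naive test. Paired analyses could mean one pair per patient at onset, a per-patient summary, a test at each visit, or a mixed model with a term for site type. The preceding paragraph shows awareness of repeated measures. The article is a condensed account, and the unit of analysis for a supporting contrast may be set out in a fuller plan that is not shown.

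Much of this stands. A reader might infer that the plan uses simple paired tests that treat every visit and lesion as independent, and so has an inflated error rate. The document does not support that: it names no test and nowhere says that pairs will be pooled. A reader might also take this contrast for the study's main within-patient evidence. That too lacks support, since the longitudinal mixed model is named as the primary approach and affected-versus-control is not a named comparison under Outcomes. The figure of 46 is a planning minimum for another comparison; the target of 165 at 1:2 would give 55. The inflation formula does not contain the number of patients, so this changes little.

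What does not stand is that only detail is missing. A method is named for this contrast, and it differs from the one given for repeated observations. As an ordinary paired test it would either mishandle the several pairs or make no use of most of them. The mixed model already in the plan, extended to this contrast, does better than both.

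**Conclusion.** The point holds as a conditional one. The design can yield several correlated pairs per patient, and the method named for comparing them is not the one in the plan that deals with such correlation. If the pairs were pooled, a nominal 5% test would have a true error of about 9–27%. That range rests on assumed values of 2–4 pairs per patient and a correlation of 0.3–0.7; the article gives neither. Pairs could be fewer, since no reading is scheduled between 96 hours and day 14. With one pair or one summary per patient there is no inflation; the cost of keeping a single pair is unused readings.

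This is a supporting contrast. The primary mixed-model analysis, the discrete-time survival analysis and the sample size are not affected. The change is worth making but is not critical.

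**What to change.** Replace the sentence on paired analyses with one of the following.

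1. **Preferred.** Analyse the affected-minus-control difference at each visit after onset in a linear mixed model, with random intercepts for patient and for lesion within patient. Report the mean difference with its confidence interval.
2. **If a paired test is kept.** Restrict it to one prespecified pair per patient (the first visit with a PI and one index lesion, with the rule for choosing that lesion stated), or to one summary difference per patient.

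Adjustment for the difference at the same site before injury is optional. It applies only where the same marked location is still being measured. From Stage II on the reading moves to adjacent skin, and a lesion outside the predefined sites would have no earlier reading.

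The cost is wider intervals than pooling would give and slightly more analysis work. No new data are needed, and the minimum of 138 stays as it is. The Study status section says that recruitment had not begun at submission, so on that account the wording can be settled before any data are seen.
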